## 4. Discontinuation of Study for Subjects by the Research Team

The study team can discontinue the subject from the study, and possible reasons for discontinuation from the study include:(1)Intolerance to oral nutritional supplements and/or specialized wound supplements such as nausea, vomiting, bloatedness, and diarrhea;(2)Allergic reaction to specialized wound supplements;(3)Frequent readmission to hospitals for wound infections that cannot be managed in the home care setting;(4)Non-compliance to supplementations or dietary advice provided;(5)Non-compliance to wound management advice;(6)Worsening of the wound requiring surgical intervention;(7)New diagnosis of diseases included in the exclusion criteria;(8)New diagnosis of infectious diseases (such as COVID-19) that requires the subject to be isolated for >7 days and prevents the research team from having access to the subject.

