### 2.4. Sample Size Estimation

The sample size calculation is based on the results reported by Cereda et al. [17], where an odds ratio (OR) of 2.0 for ≥ 40% improvement in wound area on patients receiving a specialized nutritional supplementation containing arginine is used. To have 80% power to detect this difference with a 2-tailed type I error of less than 5%, we require at least 144 subjects per arm. After assuming a 20% mortality and 10% withdrawal rate (based on a Cereda et al. [17] study of 16% mortality and 6% withdrawal and a Chaboyer et al. [22] study of 8% loss to follow-up), we plan to enroll a total of 380 subjects (190 per arm). As we will be undertaking an intention-to-treat (ITT) analysis, anticipated adherence will be one of the outcome measurements to determine if the intervention (education and supplementation) is acceptable to the participants (Supplementary Material Figure S1).

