## 5. Statistical and Analytical Plans

We will implement an intention-to-treat (ITT) analysis, meaning all subjects randomized to either the intervention or control groups will be analyzed. Subjects who withdraw or are lost to follow-up will have their data analyzed up to their last recorded home nursing visit.

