### 5.3. Subgroup Analyses

A planned subgroup analysis will be performed by targeting specific nutritional status and intake variables, route of intake (oral versus enteral), staging of PIs, gender, age group, compliance to intervention, and functional status. 

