### 5.4. Secondary Analyses

Per-protocol analyses planned include the proportion of wounds that will be executed, excluding subjects who:Suffer from wound infections;Show non-compliance to the treatment;Dropout from the trial;Die during the trial period.

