	Clinical	Mortality	Assessed by the occurrence and time-to-event of all-cause mortality during the study period.	t_1_ 30 days, t_1_ 60 days, t_3_ 90 days, and t_x_ 1 year Time frame: 1 year	Nurse, CRC
		Unplanned hospital admissions	Assessed by the occurrence and time-to-event of one or more unplanned hospital admissions during the study period.	t_1_ 30 days, t_1_ 60 days, t_3_ 90 days, and t_x_ 1 year Time frame: 1 year	Nurse, CRC
Others	Pre-specified Outcome	Adherence to nutrition Supplementation intake	Assessed by the number of participants with >75% consumption of oral nutritional supplements and Arginaid, where the servings of products consumed are counted with confirmation of intake during follow-up.	t_1_ 30 days, t_1_ 60 days, and t_3_ 90 days Time frame: 1 year	Dietitian, Nurse, CRC
		Wound depth	Measured (millimeters) using sterile forceps and rulers at follow-up.	t_0_ baseline, t_1_ 30 days, t_1_ 60 days, 90 t_3_ days, and t_x_ 1 year Time frame: 1 year	Nurse
		Hospital length of stay	Assessed by the number of days for each unplanned hospital admission.	If available: t_x_ 1 year Time frame: 1 year	Nurse, CRC
		Wound duration and time-to-heal	Measured by days to complete healing for participants with complete wound healing. Additional interaction of time with intervention and other covariates will be included and tested	t_x_ 1 year Time frame: 1 year	Investigators
		Frequency of unplanned hospital admissions	Assessed by the frequency of occurrence per participant and the sum of unplanned hospital admissions of all participants.	t_x_ 1 year	Investigators

^#^ The data from the measurement of the pressure injury with the highest severity will be used in the analysis for the primary endpoint. If the wound of the highest severity is deemed unmeasurable (e.g., too small of a surface area), we will select the wound with the next highest severity. CRC: clinical research coordinator; HRQOL: health-related quality of life; PI: pressure injury.

**Table 3 nutrients-16-00299-t003:** Study schedule of enrolment, interventions, and assessments.

	STUDY PERIOD							
	Enrollment	Allocation	Post-Allocation					Close-Out
TIMEPOINT	*−7 to −1d* −*t_0_*	Baseline *t_0_*	*30d t_1_*	*60d t_2_*	*90d t_3_*	*6m t_4_*		*1y* *t_x_*

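### Section 4 lets the study team remove participants from the study, not only from the intervention, for reasons tied to arm or outcome; this conflicts with the ITT statement and makes censoring informative

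*Protocol article*

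**What the plan says.** Section 4 of the protocol article opens: "The study team can discontinue the subject from the study, and possible reasons for discontinuation from the study include", followed by eight reasons. Reason 1 is intolerance to supplements and reason 2 is allergy to the wound supplement. Reason 3 is frequent readmission for wound infection. Reason 4 is "Non-compliance to supplementations or dietary advice provided". Reason 6 is worsening that needs surgery. The wording is permissive, and it concerns the study as a whole, not the supplement or the bundle.

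Section 5 commits to ITT analysis of everyone randomised and then states: "Subjects who withdraw or are lost to follow-up will have their data analyzed up to their last recorded home nursing visit". Section 5.1 analyses dichotomous outcomes as time-to-event data with Cox models. Section 2.4 makes adherence an outcome measure because the analysis is ITT.

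Under section 2.7, subjects, research dietitians and nursing staff know the allocation; the trial statistician does not. The specialised supplement goes only to the intervention arm (section 2.9). Controls may have high-protein, high-energy supplements and dietary advice on earlier recommendations (section 2.10).

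The per-protocol analyses in section 5.4 exclude subjects who: "Suffer from wound infections;Show non-compliance to the treatment;Dropout from the trial;Die during the trial period". Section 3.2 lists wound infection and mortality as secondary outcomes.

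**The concern.** ITT analysis needs outcomes to be collected in the allocated arm whatever happens to treatment. Section 4 ends participation for reasons that are not neutral. Allergy to the study supplement can arise only in the arm that receives it. Intolerance and supplement non-compliance will arise mainly there. Infection readmissions and worsening to the point of surgery are poor outcomes in themselves. A team that knows the allocation makes the decision at its discretion.

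If participation ends, so does observation. The Cox model treats a censored participant as having the same prospects as those still followed, which is doubtful for someone removed because the wound got worse. The loss also reaches the EQ-5D and resource-use data behind the ITT cost-effectiveness analysis in section 6.2. A later analysis plan cannot recover visits that were never made, and section 7 says that recruitment began in October 2023.

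**Working it through.** **1. The passages side by side**

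- *Section 4 against section 5.* Table 3 schedules wound assessment at baseline, days 30, 60 and 90, 6 months and 1 year. Anyone removed before the day-30 visit has no scheduled post-baseline wound measurement, so neither primary outcome can be observed. The promise to analyse everyone randomised cannot be kept for them with observed data.
- *Section 4 against section 2.4.* Adherence is an outcome to be measured under ITT, yet non-adherence is a reason for ending participation.
- *Section 4 against section 6.2.* EQ-5D is scheduled at baseline, day 90, 6 months and 1 year. Anyone removed before day 90 has only a baseline value for QALYs.

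**2. The plan's own sample size, for scale**

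Section 2.4 asks for "80% power to detect this difference" (an odds ratio of 2.0) with a "2-tailed type I error of less than 5" per cent, and arrives at 144 per arm. The control rate is not stated. Assume 40%:

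- Control odds 0.40/0.60 = 0.667; doubled, 1.333; intervention rate 1.333/2.333 = 57.1%.
- The two-proportion formula gives 133 per arm, or 144 with continuity correction. At an assumed 30% without correction it gives 141. The figure is reproducible.
- Inflation: 144 × 1.30 = 187.2, close to the planned 190. The 30% is 20% mortality plus 10% withdrawal; there is no separate term for removal by the study team.

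The point does not depend on this calculation. It supplies only the 144 per arm used below.

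**3. Effect of censoring at the last visit, with no true effect**

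All of these inputs are assumptions except the 144 per arm and the visit days:

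- 144 per arm, individually randomised, no clustering; visits at days 30, 60 and 90.
- The event is the first visit with at least 40% area reduction. The per-visit probability is logistic(−2.0 + f), with f normal, mean 0, SD 1.5, the same in both arms. About 35 to 40% respond by day 90.
- Removal comes only from the slow-healing third (lowest f), at three times the arm's stated rate, and those removed are censored at the day-30 visit.
- Log-rank test, two-sided 5%, 3,000 runs per row. Simulation error near 5% is √(0.05 × 0.95 / 3000) = 0.4 percentage points.

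| Removed, intervention | Removed, control | Mean HR | Type I error |
|---|---|---|---|
| 0% | 0% | 1.00 | 4.4% |
| 10% | 0% | 1.06 | 6.6% |
| 20% | 0% | 1.15 | 9.4% |
| 20% | 5% | 1.12 | 8.3% |
| 30% | 5% | 1.22 | 14.2% |

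With nobody removed, the error rate is nominal within simulation error. It rises with the imbalance in removals.

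**4. The opposite direction**

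Suppose the true odds ratio is 2.0 and the control rate 40%, and removed intervention participants would have responded at their arm's rate but are counted as non-responders:

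- 10% removed: 0.571 × 0.90 = 0.514; OR = (0.514/0.486)/0.667 = 1.59; power 50%.
- 20% removed: 0.571 × 0.80 = 0.457; OR = (0.457/0.543)/0.667 = 1.26; power 16%.
- None removed: power 83%.

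The direction therefore depends on who is removed and how they enter the analysis. The documents fix neither.

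**The case against.** **A condensed article.** Section 8.3 promises a description of events that would prevent a participant from continuing the intervention, so the full protocol may already separate stopping treatment from leaving the study. That is possible. But section 4 as published says the study, in both its heading and its text, and no section says that visits continue.

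**Discretion and inference.** Removal is optional, and section 5 names those who withdraw or are lost, not those removed by the team. Applying its last-visit rule to them is an inference. It is the natural one, since no other rule covers them, and their later data would be missing in any case.

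**Stronger readings that the documents do not support.**

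- *That failures are dropped from the ITT set.* Section 5 keeps everyone in the analysis, and section 5.1 uses time-to-event methods. The text implies censoring, not deletion, so calculations that delete these participants overstate the effect.
- *That the bias favours the intervention.* Only allergy is exclusive to one arm. Intolerance and non-compliance can also occur in controls who take supplements or receive advice, and the remaining reasons apply to both arms.
- *That other analyses also break ITT.* The per-protocol set (section 5.4), the subgroup by "compliance to intervention, and functional status" (section 5.3) and the time-to-heal row of Table 2 ("Measured by days to complete healing for participants with complete wound healing") are labelled separately from the ITT analysis. Complete healing is also a dichotomous outcome, to which section 5.1 applies time-to-event analysis.

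One narrower criticism stands: the per-protocol exclusions for infection and death condition on trial outcomes that treatment may affect.

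**Conclusion.** The point holds as an internal conflict with a real cost in data. Section 4 allows removal from the study for reasons related to arm or outcome, and no section provides for continued follow-up. That cannot be squared with the ITT commitment in section 5 or with adherence as an outcome in section 2.4. Followed as written, it loses later outcomes and makes censoring informative for the primary comparison.

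The size is not known, because the documents give no removal rates. Under the assumptions shown, with no true effect and removals of 10% or 20% from the slow-healing third of the intervention arm only, the hazard ratio is 1.06 or 1.15 and the type I error about 6.6% or 9.4%. Other assumptions would pull the estimate towards no effect. The supported conclusion is bias of unknown direction and modest to material size, not a bias known to favour the intervention. It is worth correcting promptly, because the missing visits cannot be recovered. The per-protocol exclusions are a minor, separate matter.

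**What to change.** - **Section 4:** distinguish stopping the supplement or bundle from leaving the study. Leave the clinical reasons for stopping as they are. State that participants who stop remain in scheduled wound, EQ-5D, admission and mortality follow-up to 1 year, where access is possible and consent has not been withdrawn.
- **Section 5:** state that these participants are analysed in their allocated arm with all data collected after discontinuation, and that the last-visit rule applies only where no later data could be obtained.
- **Section 2.4:** reconcile with the revised section 4, so that non-adherence is measured and does not end follow-up.
- **Section 5.4 (minor):** drop wound infection and death as per-protocol exclusions and define the set by adherence.

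The cost is an amendment to the wording and slightly more follow-up data to collect. Some visits will remain impossible, for example during the isolation in reason 8 or some hospital stays under reason 3. The 144 per arm does not change.

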## 5. Statistical and Analytical Plans

We will implement an intention-to-treat (ITT) analysis, meaning all subjects randomized to either the intervention or control groups will be analyzed. Subjects who withdraw or are lost to follow-up will have their data analyzed up to their last recorded home nursing visit.

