## 1. Background

A pressure injury (PI) is defined as a “localized injury to the skin and/or underlying tissue usually over a bony prominence, as a result of pressure, or pressure in combination with shear” [1]. In Singapore, the majority of adults with stage III to IV PIs were community-acquired, [2] with a prevalence of 6% to 29% reported [3]. An incidence rate of 505 (95% CI: 493–517) per 100,000 persons has been reported, and it has been observed to increase with age, with the sharpest rise observed in individuals aged 80 years and above, at 3647 (95% CI: 3530–3766) per 100,000 persons [3,4].

PI(s) are associated with increased morbidity and mortality. Zhan and Miller [5] reported 3.98 days of extra hospitalization (*p* < 0.001) and 7.23% excess mortality (*p* < 0.001). Locally, one-fifth (20.0%) of patients had two or more PI-related readmissions for the index wound [6]. On subsequent follow-up one year later, the all-cause mortality rate was 14.3%, with 26.8% of patients institutionalized upon discharge from the tertiary hospital [6]. 

The most recent 2014 Cochrane review found no clear evidence that nutritional interventions reduce/heal PI(s) [7], but newer studies in recent years indicated potential benefits of using specialized nutritional feeds containing specific amino acids, such as arginine and leucine, as well as antioxidants, such as Vitamins C and E [8,9,10,11]. 

Integrated care is still in its development stages in Singapore and Asian countries, in comparison to the countries in North America and Europe [12]. Patients with PIs in Singapore are routinely reviewed by dietitians in acute care settings but rarely in the community upon discharge. This may be related to the failure to return for outpatient clinic reviews due to immobility and social reasons [13]. Furthermore, there is limited access to community dietitians and funding for dietetic review or nutritional support [14]. Most patients and their caregivers/family members also do not receive adequate nutritional education on PI treatment and prevention, as it is not a standard procedure in most healthcare settings. As a result, the majority of patients or caregivers do not have the necessary nutritional knowledge for PI management. 

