### 2.1. Study Design

We intend to perform a two-group, non-blinded, cluster randomized, and pragmatic clinical trial with the recruitment of 380 subjects (190 per arm). The duration of the intervention will be 90 days, with data collection of outcomes performed over a one (1)-year period. 

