### 3.1. Primary Outcome Measurements 

Change in Pressure Injury Area from the Baseline: Measurement of the alteration in the surface area of the identified pressure injury (PI) at identified time points;Proportion of Participants with 40% or Greater Area Reduction: Calculation of the percentage of participants who exhibit a reduction in the PI area by at least 40% at the same time points.

For participants with multiple PIs, the most severe or largest same-stage PI will be selected for primary analyses. Data from additional PIs will contribute to secondary analyses. Assessments and treatment documentation will be conducted during scheduled home nursing visits. Both objective and patient-reported outcome measures are used for the secondary outcome measurements to ensure that crucial additional information is collected from the participant’s perspective. 

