### 6.2. Cost-Effectiveness Analysis 

The primary outcome will be based on an intention-to-treat (ITT) principle for the CEA. The change to total costs will be compared to the change to health benefits, as measured by quality-adjusted life years (QALYs). Total costs will be estimated by considering the extra costs of the intervention and the change to the use of health services in subsequent time periods. QALY outcomes will be estimated using data from the EQ5D-5L, and the change due to the intervention will be estimated. Uncertainty will be included in probabilistic sensitivity analysis.

The incremental mean costs will be estimated from participants in both groups based on resource unit cost multiplied by resource utilization. The change to total costs and QALYs will be considered on the cost-effectiveness plane and analyzed quantitatively to estimate the probability that the adoption of intervention is a good decision against maximum willingness to pay thresholds for marginal health benefits, such as QALYs. Further details of the economic evaluation protocol are available in the Supplementary Material.

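### For subjects who withdraw or are lost, ending all data at the last home nursing visit discards known later deaths and unplanned admissions, which are defined over one year and need no home visit

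*Protocol article*

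**What the plan says.** Section 5 of the protocol article announces an intention-to-treat analysis, "meaning all subjects randomized to either the intervention or control groups will be analyzed", and adds: "Subjects who withdraw or are lost to follow-up will have their data analyzed up to their last recorded home nursing visit". The second sentence makes no distinction between outcomes.

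On follow-up, Section 2.1 states: "The duration of the intervention will be 90 days, with data collection of outcomes performed over a one (1)-year period". On where data are gathered, Section 3.1 states: "Assessments and treatment documentation will be conducted during scheduled home nursing visits".

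Table 2 defines mortality as "Assessed by the occurrence and time-to-event of all-cause mortality during the study period" and unplanned admissions as "Assessed by the occurrence and time-to-event of one or more unplanned hospital admissions during the study period". Both have a one-year time frame and are assigned to the nurse and the CRC. Length of stay (nurse and CRC) and admission frequency (investigators) are compiled at one year.

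Section 5.1 analyses dichotomous outcomes by time-to-event methods with Cox models. Section 4 lets the team discontinue a subject from the study for reasons that include frequent readmission for wound infection, a worsening wound that needs surgery, supplement intolerance or allergy, and non-compliance. It does not say whether outcomes are still collected afterwards. On the economic evaluation, Section 6.2 states: "The primary outcome will be based on an intention-to-treat (ITT) principle for the CEA".

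**The concern.** A home nursing visit is an event in the delivery of care. It is a sensible last data point for a wound image or a nutritional assessment, because nothing can be measured without one. It is a poor last data point for death or hospital admission, which can be established by telephone or from records after the visits stop.

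Two things are at stake. First, a death or admission that the CRC has on file would be left out if it came after the last home visit of a withdrawn or lost subject. Retaining that subject in the analysis set does not repair the loss of a known event. Second, the Cox model assumes that censoring carries no information about later risk. If subjects stop being visited because they are deteriorating, censoring them at the last visit removes follow-up from those most likely to have the event. If the reasons for stopping differ by arm, the hazard ratio itself may be biased.

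**Working it through.** The point rests on setting the sections against each other. The arithmetic only gives scale.

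**Step 1. Scope of the rule.** Section 5 applies the cut-off to subjects who withdraw or are lost, and to no one else. Within that group it covers every outcome.

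**Step 2. Does each outcome need a home visit?**

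| Outcome | Source in the protocol article | Home visit needed? |
|---|---|---|
| Wound area, stage, depth | Table 2 (3D imaging, clinical assessment, ruler) | Yes |
| Nutritional status | Table 2 (GLIM) | Yes |
| All-cause mortality, 1 year | Table 2 (nurse, CRC) | No |
| Unplanned admissions, 1 year | Table 2 (nurse, CRC) | No |
| Length of stay | Table 2 (nurse, CRC, at 1 year) | No |

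For the first two rows the rule costs nothing that could have been observed. For the last three it conflicts with the definition over the study period.

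**Step 3. Could the censoring be informative?** Section 3.1 ties assessments to home nursing visits. Section 4 lists outcome-related reasons for discontinuation (readmission, worsening wound). It also lists reasons that arise mainly or only in the intervention arm: the specialised wound supplement is given only there (Section 2.9), while controls continue on earlier recommendations (Section 2.10). If discontinued subjects are treated as withdrawn, Section 5 cuts them off at a point related to outcome and, in part, to arm. The article does not say whether they are so treated.

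**Step 4. Scale.** Inputs: 144 per arm required, 20% mortality, 10% withdrawal, 190 per arm, 380 in total (all Section 2.4).

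- The plan's enrolment figure reproduces as 144 × 1.2 × 1.1 = 190.08, so withdrawal is budgeted separately from death.
- Planned withdrawals: 0.10 × 380 = 38 subjects.
- Share of the one-year window lost per withdrawn subject = 1 − d/365, where d is the day of the last visit. The document gives no value for d, so a range is assumed.
- Share of all planned person-time lost = 0.10 × (1 − d/365), ignoring deaths.

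| Assumed last visit (day) | Window lost per subject | Planned person-time lost |
|---|---|---|
| 30 | 0.918 | 0.092 |
| 60 | 0.836 | 0.084 |
| 90 | 0.753 | 0.075 |
| 182 | 0.501 | 0.050 |

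About 5% to 9% of planned follow-up for mortality and admissions is therefore exposed to the rule. How many events fall in that time, and how they split by arm, cannot be derived from the document.

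**The case against.** The strongest reply is that keeping every randomised subject and using data up to last contact for those truly lost is common, and does not by itself contradict intention to treat. A subject whose death the CRC records is arguably not lost for that outcome at all. This stands in part. If that is what the authors mean, the defect is one of wording. But a home nursing visit is narrower than last contact, the sentence is not outcome-specific, and a subject who has withdrawn falls under it even when vital status is known.

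A reader might also infer several stronger points that the document does not support:

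- *That the cut-off governs everyone who is hospitalised, institutionalised or healed.* No section says such participants count as withdrawn or lost, and Table 2 plans admission and healing outcomes to one year.
- *That healed status is lost.* Under the time-to-event analysis in Section 5.1, healing recorded at or before the last visit is kept as an event.
- *That QALYs and costs are truncated at the last visit.* Section 6.2 does not say so. It includes later health-service use and refers further detail to supplementary material that is not shown.
- *That the Background figures show how often this happens.* The cohort "with 26.8% of patients institutionalized upon discharge from the tertiary hospital" was a hospital one. The trial enrols people living in the community, and the figure is not an in-trial exit rate.

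**Conclusion.** The concern holds in a narrow form. For subjects who withdraw or are lost, Section 5 ends all data at a home nursing visit, which conflicts with the one-year definitions of mortality and unplanned admissions in Table 2. Applied literally, it discards known events and censors at a point that may be informative.

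The informative-censoring part is conditional. It is strongest if subjects discontinued under Section 4 are treated as withdrawn, which the article leaves open. The economic part is conditional too: Section 6.2 claims an intention-to-treat basis and does not adopt the cut-off, but nothing in the article prevents it from being carried over.

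The bias cannot be quantified from the document. The planned 38 withdrawals, with 5% to 9% of person-time exposed under the assumed last-visit days, show that it is neither negligible nor dominant. The effect falls on secondary outcomes. Wound measurements, and so the primary clinical outcomes, need an assessment and are not harmed by this limit.

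**What to change.** Replace the single sentence in Section 5 with outcome-specific cut-offs:

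1. Keep the last home nursing visit as the limit only for outcomes that need a home assessment (wound measurements, nutritional assessment).
2. For mortality, unplanned admissions and length of stay, include all events to one year, from records or CRC contact, for every randomised subject who has not withdrawn consent to such data. Otherwise censor at the last known-alive date (mortality) or last-ascertained date (admissions).
3. State that subjects discontinued under Section 4 stay in outcome follow-up.
4. Reconcile Section 5 with Section 4, Section 6.2 and Table 2, so that the intention-to-treat cost-effectiveness analysis does not inherit the home-visit cut-off.

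The cost is a few sentences and a little extra record checking. Table 2 already assigns these outcomes to the nurse and CRC. Whether the consent form covers access to records should be checked, since it is in the supplement that is not shown.
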